### Evaluation of outcomes

The two-sample *t* test will be used for analysis of continuous variables. The chi-square test will be used for analysis of categorical variables and for all data, a *p* value <0.05 will be considered significant. The software program SPSS will be used for all statistical analysis. Subgroup analysis based on the severity of the fractures will also be conducted. Patients will be analysed as per their treatment but non adherence will be considered in the final presentation of data. An interim analysis will be also be undertaken. There are no other audits of trial conduct planned.

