## Methods

### Study objectives

The primary objective of the trial is to determine if intraoperative CT imaging improves clinical outcomes for zygomaticomaxillary complex and zygomatic arch fractures that are managed surgically. This will be assessed through the following variables:
Post-operative radiographic reduction adequacyNeed for revision surgeryNumber of intra-operative re-reductionsPost-operative diplopiaFacial profile restorationSurgical incision and scarring

The secondary objective of the trial is to ascertain whether intraoperative CT imaging has a significant impact on the length of surgery and whether it affects the outcomes of delayed versus early surgical treatment outcomes [15].

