### Power calculation

An estimated 200 patients will be required for a sample size that will produce significant results. This is based on two-sided testing with a power calculation of 80% and is established from local department outcome estimates and results from studies by Van Hout et al., Hurrell et al. and Van Den Bergh et al. [10, 15, 16]. The variable that required the largest projected sample size to obtain a statistically significant result was the adequacy of post-operative fracture reduction as demonstrated radiographically. The power calculation was performed by [name], a biostatistician from the University of Queensland (UQ) School of Population Health.

Due to the low level of evidence available in the current literature, the sample size calculations may not be reliable and estimates were not possible for all variables being proposed in this study. Subsequently, a mid-study analysis will be conducted to more accurately assess the predicted sample size calculations. It is estimated that from the average number patients presenting yearly with ZMC and ZA fractures at the RBWH, this study will take approximately 2 years to complete. If the mid-study analysis identifies a statistically significant result, the study will potentially be terminated early. The decision to terminate the trial or continue after the mid-study analysis will be at the discretion of the study authors.

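### One blanket p<0.05 rule, with only the t test and chi-square test, puts fracture-severity subgroup results on the same footing as the overall comparison and cannot show that the CT effect differs by severity

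*Protocol article*

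**What the plan says.** The section Evaluation of outcomes assigns the two-sample t test to continuous variables. For the rest it says "The chi-square test will be used for analysis of categorical variables", and the same sentence goes on to fix the significance level: "for all data, a *p* value <0.05 will be considered significant". Two sentences later comes the whole of the subgroup plan: "Subgroup analysis based on the severity of the fractures will also be conducted". The section does not define severity, the number of levels or the outcomes to be examined, and it exempts nothing from the threshold.

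The section Power calculation states "An estimated 200 patients will be required for a sample size that will produce significant results", with two-sided testing and 80% power. It identifies the driver of that number: "The variable that required the largest projected sample size to obtain a statistically significant result was the adequacy of post-operative fracture reduction", as seen on radiographs. Subgroups are not mentioned there. The section also warns that the calculations may be unreliable.

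The section Study objectives lists six variables under the primary objective, without ranking them; radiographic reduction adequacy is the first.

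**The concern.** The threshold covers all data without exception, and the only tools named are two-group tests. Applied to severity subgroups, these give a CT-versus-control test within each level at the full 0.05. Two errors follow.

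- **False positive in a level.** If CT has no effect, each added level is another chance of a significant result, and the stated rule gives that result the same standing as the overall one.
- **False contrast between levels.** If CT has the same effect at every severity, the smaller samples within levels will often give significance in one and not in another. That looks like a differential effect but is not evidence of one. Only a direct comparison of the effects, that is an interaction, addresses the question, and neither named test does this.

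Either error could lead to intra-operative CT being recommended for, or withheld from, patients by fracture severity on the strength of chance. The article itself puts the price of the scan at about 10 extra minutes of surgery and an estimated 1.5 mSv against 0.4 mSv, so a wrong recommendation in either direction matters.

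**Working it through.** **Inputs from the article.** Alpha 0.05 for all data (Evaluation of outcomes). Two-sided testing, 80% power and a total of 200, driven by radiographic reduction adequacy (Power calculation). Six variables under the primary objective (Study objectives). Two groups, about 1:1 (Randomisation).

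**Assumptions, because the article does not say.** Two or three severity levels; equal sizes unless stated; arms balanced within levels; normal approximation.

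**The plan's own figure.** The total of 200 cannot be reproduced, because no rates or effect size are given. Many pairs of rates would fit about 100 per arm. One example is 75% versus 90%, with mean 0.825, using n = [1.96·√(2·p̄·(1−p̄)) + 0.842·√(p1(1−p1) + p2(1−p2))]² / (p2−p1)²:

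- n = [1.96·√0.28875 + 0.842·√0.2775]² / 0.15² ≈ 99.5, so 100 per arm.

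The pairs 70% versus 86.3% and 80% versus 93.4% also give 100. Nothing below depends on which pair was used.

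**Step 1. False subgroup result with no CT effect, one outcome.** Levels contain different patients, so the tests are independent: P(at least one) = 1 − 0.95^s.

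- s = 2: 1 − 0.9025 = 0.098
- s = 3: 1 − 0.8574 = 0.143

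These are 2.0 and 2.9 times the stated 5%.

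**Step 2. The same if all six variables were examined.** This needs a baseline, since six outcomes inflate the error with no subgroups at all. Independent outcomes follow 1 − 0.95^(6s). The correlated cases come from simulating six equally correlated normal test statistics, giving f per level, then 1 − (1 − f)^s across levels.

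| Correlation between outcomes | No subgroups (f) | 2 levels | 3 levels |
|---|---|---|---|
| 0 | 26.5% | 46.0% | 60.3% |
| 0.5 | 20.7% | 37.0% | 50.1% |
| 0.8 | 13.9% | 25.8% | 36.2% |

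Only the rise from the second column to the third or fourth belongs to subgrouping.

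**Step 3. Disagreement between levels when the true effect is identical.** With 80% power overall, the expected z statistic is 1.96 + 0.842 = 2.80. A level holding a fraction w of the patients has expected z = 2.80·√w and power Φ(2.80·√w − 1.96).

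- Two halves: 2.80/√2 = 1.98, power Φ(0.02) = 0.508. P(exactly one significant) = 2 × 0.508 × 0.492 = 0.50.
- Three thirds: 2.80/√3 = 1.62, power Φ(−0.34) = 0.366. P(mixed results) = 1 − 0.366³ − 0.634³ = 0.70.

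Two sensitivity checks, both with two levels:

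- A 70:30 split (illustrative): powers 0.650 and 0.335, so 0.650 × 0.665 + 0.350 × 0.335 = 0.55.
- Overall power of 60% or 90% with equal halves: expected z 2.21 or 3.24, power per half 0.346 or 0.630, disagreement 2 × 0.346 × 0.654 = 0.45 or 2 × 0.630 × 0.370 = 0.47.

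**Step 4. What an interaction test could detect.** With two equal halves, the difference between the two effects has twice the standard error of the overall effect. For a difference as large as the overall effect, the expected z is 2.80/2 = 1.40 and power is Φ(1.40 − 1.96) = 0.288. With no true difference, its false-positive rate is 5%.

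**The case against.** The strongest reply is that most of this is silence in a condensed article. The definition of severity, the subgroup model, an interaction test and an exploratory label are all things that a full protocol or analysis plan, not shown here, commonly supplies. The threshold comes before the subgroup sentence, and an interaction p-value could equally be judged at 0.05, so the article does not expressly commit to separate tests within levels. This stands as far as it goes: a missing label or interaction test would not by itself be a fault here. What it does not answer is the text that is present. The rule covers all data without exception and the only tests named are two-group tests, so an analysis plan that treated the subgroups differently would have to depart from the article.

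A reader might infer more: that every listed variable will be tested in every level, and that false subgroup claims are therefore likely. The article does not support this. It names no subgroup outcomes and no number of levels. The larger six-variable figures also carry the trial's separate multiple-outcome problem, already about 21% to 26% without subgroups at correlations of 0.5 to 0. And they treat the number of intra-operative re-reductions as a null outcome, although under Study groups a difference could arise simply because the scan prompts re-reduction.

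A reader might also infer that a subgroup p-value could stop the trial early. Power calculation ties termination to a significant result at the mid-study analysis and does not mention subgroups, so this is not part of the point.

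It can also be said that the disagreement figure assumes exactly 80% power and equal levels, while the article doubts its own sample size. That is fair, but the figure moves little: 45% to 55% for two levels over the cases tried.

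**Conclusion.** The point holds in a limited form. The article fixes one threshold and two tests for everything and makes no distinction between severity subgroups and the main comparison. As written, that gives a within-level p<0.05 full standing, and the named tests cannot show that the effect of CT varies with severity.

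For radiographic reduction alone in two or three levels, the chance of at least one false subgroup result is about 10% or 14% rather than 5%; it would be higher with more outcomes. This rests on an assumed number of levels and no CT effect. With a uniform true effect and 80% overall power, two equal levels would disagree in significance about 50% of the time. That figure concerns a single outcome and needs no assumption about how many outcomes are tested.

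The text does not establish that every variable will be tested by severity, or that a false subgroup claim is more likely than not. The point is worth correcting, but it does not affect the validity of the overall comparison.

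**What to change.** Confine the p<0.05 rule in Evaluation of outcomes to the overall comparison of the two groups, and replace the subgroup sentence with wording such as:

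*Analysis by fracture severity, with severity defined from pre-operative information, is exploratory. For radiographic reduction adequacy, a treatment-by-severity interaction will be assessed in a regression model suited to the three ordered grades (for example ordinal logistic regression). The treatment effect and its 95% confidence interval will be reported for each severity level. No p-value within a severity level will be declared significant.*

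The cost is a short change of wording and one further model. The real downside is that no confirmatory claim can be made for a severity subgroup. The interaction test is also weak: about 29% power for an interaction as large as the overall effect, with two equal levels. A non-significant interaction must therefore not be read as showing that the effect is the same at every severity, and the intervals should carry the interpretation. Little is given up, since the 200 patients were sized on the overall comparison and each of two equal levels would have only about 51% power.

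### Fracture severity is used only for a subgroup analysis: the named between-arm tests are unadjusted and no group-by-severity interaction test is named, which forgoes a possible gain in precision and invites a false subgroup contrast

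*Protocol article*

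**What the plan says.** The analysis is set out in the Protocol article under Evaluation of outcomes. Continuous variables get a two-sample t test. For the rest, "The chi-square test will be used for analysis of categorical variables and for all data, a *p* value <0.05 will be considered significant". Severity appears once, in the same paragraph: "Subgroup analysis based on the severity of the fractures will also be conducted". The article names no covariate, stratified test or interaction test. It does not define severity, say how many levels it has, or say when it is graded.

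Under Randomisation, each patient is allocated by one draw from two balls, with no stratification described.

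Under Power calculation, the total is 200 patients for two-sided testing at 80% power, and one outcome set that number: "The variable that required the largest projected sample size to obtain a statistically significant result was the adequacy of post-operative fracture reduction". The assumed rates are not printed. They are described only as "established from local department outcome estimates and results from studies by" three cited publications. Under Follow up and outcomes, that outcome is graded good, fair or poor.

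**The concern.** The plan treats severity as important enough to split the sample, but the named tests cannot use it in the overall comparison. Two things follow.

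- **Overall comparison.** If severity predicts the reduction grade, adjusting for it would sharpen the estimate on the outcome that set the sample size and would correct for chance imbalance between arms. The Power calculation section itself warns that the sample size may be unreliable, so precision available at almost no cost is worth having.
- **Subgroups.** The only tests named are between-arm tests at 0.05. Applied within each severity group, they say whether each group reaches significance alone. They do not say whether the effect differs between groups. A result that is significant in one group and not in the other is easily read as a reason to scan only one kind of fracture, although it can arise by chance under one common effect.

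**Working it through.** **Inputs from the article:** N = 200, about 100 per arm; two-sided testing; 80% power; significance level 0.05; 1:1 allocation in expectation. **Not in the article, so assumed:** arm rates, number and size of severity groups, and the link between severity and reduction grade.

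**1. The plan's own figure.** N = 200 cannot be reproduced without arm rates. Solving backwards, 100 per arm gives 80% power for about 50% v 69%, 60% v 78%, 70% v 86% or 80% v 93% (no continuity correction), that is, differences of about 13 to 19 points. I take the stated 80% as given. The expected test statistic is then 1.960 + 0.842 = 2.802.

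**2. What adjustment could add.** Good v not good was simulated with N = 200, half the patients severe, simple randomisation and a common odds ratio set so that the unadjusted test has about 80% power. The comparator is a severity-stratified Cochran-Mantel-Haenszel test.

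| Control good rate, mild / severe | Gap (points) | Unadjusted | Stratified |
|---|---|---|---|
| 80% / 60% | 20 | 79.8% | 81.0% |
| 85% / 55% | 30 | 79.9% | 82.7% |
| 90% / 50% | 40 | 79.8% | 85.1% |
| 90% / 40% | 50 | 79.6% | 87.5% |

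A second set fixed the odds ratio at 2.7. Unadjusted v stratified power was 81.1% v 80.6% with no gap, 80.3% v 80.2% at 10 points, 78.5% v 79.6% at 20, 75.2% v 77.8% at 30 and 69.7% v 75.6% at 40. In both sets both tests rejected a true null about 5% of the time.

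The gain is therefore nil for gaps up to 10 points, about 1 to 3 points for gaps of 20 to 30, and about 5 to 6 at a gap of 40. Only the extreme 50-point gap gives about 8.

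**3. Chance imbalance in severity.** With half the patients severe, the SD of the between-arm difference in percent severe is √(0.25 × 4 / 200) = 7.1 points. A difference of 10 points or more is 1.41 SDs, with probability 0.157, or about 16% of trials. With a 20 to 30 point gap it moves the observed difference in good rates by 0.10 × 20 to 0.10 × 30 = 2 to 3 points.

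**4. Subgroups tested separately, same true effect in each.** Power in a fraction f of the sample is Φ(2.802 × √f − 1.960).

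- Two equal halves: Φ(1.981 − 1.960) = 0.508 each. P(exactly one significant) = 2 × 0.508 × 0.492 = 0.50.
- 30/70 split: 0.335 and 0.650; exactly one significant 0.55. 20/80 split: 0.240 and 0.707; 0.61.
- Three equal groups: 0.366 each; results disagree with probability 1 − 0.366³ − 0.634³ = 0.70.
- No true effect: P(at least one false positive) = 1 − 0.95² = 9.8% for two groups and 1 − 0.95³ = 14.3% for three.

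**5. The interaction test.** Under a uniform effect it gives a false contrast 5% of the time, against about 50% for comparing two p values. Its limit is power. With two equal halves, the difference between the two effects has twice the standard error of the overall effect. A true difference as large as the overall effect is then detected with probability Φ(2.802 / 2 − 1.960) = Φ(−0.559) = 0.29.

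**The case against.** **Covariates and interaction tests are usually left to an analysis plan, which is not shown.** This stands in part. A reader might infer that severity will never be used for adjustment, and a condensed article cannot establish that. But the article is not silent. It fixes the tests and the threshold for all data and assigns severity one role, and that stated choice is what is questioned here.

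**An unadjusted comparison in a randomised trial is valid.** This stands fully. A reader might infer that the main test loses power. The article does not support that: the only tests it names are unadjusted, and if 200 was sized for them, nothing falls below plan. The fall to 69.7% in the second simulation set is not a shortfall either. A fixed odds ratio within strata implies a smaller overall difference as the strata move apart. Only the contrast between the two tests is informative, and it may be negligible. The exclusion of other facial fractures and bilateral zygomatic fractures may also narrow the severity range, so a 40-point gap is not a default expectation.

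**Severity may not be available for every patient.** This stands. A severity subgroup analysis requires a classification, but the article does not say that one is recorded for all. The assessment forms are figures not shown here. Nor can one rule out that severity means ZMC versus isolated arch, the only fracture classification the article gives.

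**Separate within-group tests are not stated.** This also stands. They are an inference from the only tests named, and the 50% figure is conditional on them.

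**Conclusion.** The point holds in a limited form. The named analysis gives severity a subgroup role only, with no adjusted comparison and no interaction test, and allocation does not balance it. On the overall comparison this is a forgone gain rather than an error: about 0 to 6 power points for good versus not good with severity gaps up to 40 points, on assumed rates. Chance imbalance is a minor part of it, because the 5% error rate already allows for it.

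The subgroup part carries more weight because it needs no assumption about how prognostic severity is. It rests on a uniform effect, 80% power overall and separate testing at 0.05. On that basis a discordant pair of results is about as likely as not with two equal groups, and more likely with unequal or three groups. The change is worth making because it costs little and protects a conclusion that could affect who is scanned.

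**What to change.** In Evaluation of outcomes:

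1. Define fracture severity, with its levels, from pre-operative imaging, graded without knowledge of study group, so that the intervention cannot affect it.
2. Make the main comparison of radiographic reduction severity-adjusted: ordinal logistic regression of good/fair/poor on study group and severity or, if few patients are graded poor, a severity-stratified test of good versus not good. Keep the unadjusted chi-square as a supporting analysis.
3. Assess subgroups by a group-by-severity interaction test. Report the effect with its confidence interval at each severity level as exploratory, and do not interpret separate subgroup p values. State that a non-significant interaction does not show equal effects, given the low power shown above.

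The cost is a few sentences and a little more SPSS work, with no extra patients. If severity is not already graded for every patient, pre-operative images must be read for it; the article does not describe these images, so their availability is an assumption. The odds ratio also becomes conditional on severity and will not match the crude one. The change should be fixed before any unblinded look at outcomes by arm, including the planned mid-study analysis if that has not yet taken place.

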### Randomisation

The patients who are recruited to the trial will be randomised into two groups, intraoperative computed tomography scan (intervention) and no intraoperative computed tomography scan (control). The patient will be randomised by the oral and maxillofacial surgery department nurse, who will blindly select a table tennis ball from a container. The container will hold only two balls, with one ball having the word “intervention” and the other ball having the word “control” written on them. Whichever ball is selected by the nurse, is the group to which the patient is allocated.

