### Blinding

The patients will not be informed of the group to which they are randomised. Concurrently, the clinician assessing the fracture reduction on the post-operative radiographs will be blinded to the arm of the trial to which the patient has been allocated. The surgeon operating on the patient will not be blinded as this is impossible, given they will be witness to whether or not intra-operative CT is performed. The physician assessing the patient in clinic at both 1 week and 6 weeks post-surgery will not be blinded to the patient’s study group. Blinding of this assessment would be extremely difficult as the physician assessing the patient will be involved with the operation and hence know the allocated group. The clinician assessing the post-operative radiographic reduction will not perform any of the operations in the trial.

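### The stated rule most naturally compares patients by treatment received, with no analysis by allocated group, so non-adherence related to fracture difficulty would bias the comparison

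*Protocol article*

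**What the plan says.** The only statement of how patients are grouped for analysis is in Methods, Evaluation of outcomes: "Patients will be analysed as per their treatment but non adherence will be considered in the final presentation of data". No section names an intention-to-treat or as-randomised analysis, either as the main analysis or as a sensitivity analysis.

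The same section fixes the tests. A two-sample t test is used for continuous variables, and "The chi-square test will be used for analysis of categorical variables". Neither adjusts for fracture severity, which appears only as a subgroup analysis.

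Two other sections bear on whether treatment could differ from allocation:

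- **Study groups:** CT is assigned to the whole intervention group, and intra-operative imaging is ruled out for controls. The surgeon's stated discretion over scanning concerns a repeat scan in an intervention patient whose reduction has been corrected.
- **Blinding:** "The surgeon operating on the patient will not be blinded as this is impossible". The surgeon therefore knows which arm the patient is in.

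**The concern.** Treatment received and treatment allocated differ only where there is non-adherence. The sentence sets grouping by treatment against a promise to consider non-adherence at presentation, and that contrast makes most sense if the treatment meant is the one received.

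Patients who deviate would then change comparison groups. The article's own case for CT is that limited exposure makes the reduction hard to judge. If a control patient were scanned despite the protocol, a difficult or doubtful reduction is a plausible reason. Difficulty plausibly also lowers the radiographic grade. The group that received CT would gain harder cases and the other group would lose them, and an unadjusted test would read the shift in case mix as an effect of CT.

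The main comparison is at stake. So may be the mid-study look: the Power calculation section allows early termination on a significant result, and if the same grouping rule governs that look, a confounded p value could feed the decision.

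**Working it through.** **1. The plan's own figure.** The Power calculation section gives 200 patients in total, two-sided testing and 80% power, driven by radiographic adequacy of reduction. It states no rates, so 200 can be neither reproduced nor refuted. It is attainable. For example, for 75% against 90%:

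n per arm = [1.96 × √(2 × 0.825 × 0.175) + 0.842 × √(0.75 × 0.25 + 0.90 × 0.10)]² / 0.15² = (1.053 + 0.443)² / 0.0225 ≈ 99.5, so 100 per arm and 200 in total.

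Only the total is used below.

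**2. Inputs.**

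- From the article: 200 patients; one of two balls drawn per patient, so about 100 per arm in expectation; chi-square test; significance at p < 0.05.
- Assumed, because the article gives none of these: no true CT effect; 20% difficult fractures with 30% graded good; 80% other fractures with 80% graded good; only difficult control patients cross over. The overall rate of good reductions is 0.2 × 0.30 + 0.8 × 0.80 = 0.70 in both arms.

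**3. Bias.** If k of 100 controls cross, each with a 30% chance of a good grade:

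- received CT: (70 + 0.3k) / (100 + k)
- no CT: (70 − 0.3k) / (100 − k)
- difference: −80k / (10,000 − k²)

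**4. False rejections.** For the uncorrected chi-square test, by normal approximation:

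Φ((|d| − 1.96 s0)/s1) + Φ((−|d| − 1.96 s0)/s1)

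Here s0 is the standard error pooled at 0.70 and s1 is the unpooled one. For k = 10, d = −0.0808, s0 = √(0.21 × (1/110 + 1/90)) = 0.0651 and s1 = 0.0644. The two terms are 0.2333 and 0.0006, together 23.4%.

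| Controls crossing (of 100) | Good, CT received | Good, no CT | Difference | False rejections, formula | Simulation |
|---|---|---|---|---|---|
| 0 | 70.0% | 70.0% | 0 | 5.0% | about 5% |
| 2 | 69.2% | 70.8% | −1.6 points | 5.7% | about 6% |
| 5 | 68.1% | 72.1% | −4.0 points | 9.4% | about 9% |
| 10 | 66.4% | 74.4% | −8.1 points | 23.4% | about 23% |
| 15 | 64.8% | 77.1% | −12.3 points | 46.4% | about 47% |

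Simulated trials analysed by allocation rejected in 4.5% to 5.4% of cases, with an expected difference of zero in every row.

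**5. A milder case mix.** With 30% difficult fractures and adequate reduction in 90% of easy and 60% of difficult cases, 3, 6, 10 and 15 controls crossing give −1.3, −2.5, −4.2 and −6.4 points. False rejections are about 5.6%, 7.3%, 12% and 20%. The direction is the same and the size smaller.

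**6. Direction.** In the first case mix, the share of null trials that falsely favour CT is the second term of the formula. It falls from 2.5% with no crossover to 0.5% with 5 crossing and 0.06% with 10 crossing. The excess rejections are all against CT.

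**The case against.** The strongest reply is that the protocol opens no route to crossover. Controls are to have no intra-operative imaging, and the Ethical considerations section repeats this. A reader might infer from the Blinding section that the surgeon chooses in theatre who is scanned. The text does not support that: it says only that the surgeon will see whether CT is done, and the scanning discretion in the Study groups section cannot move a patient between arms. This part of the reply stands, so any crossover modelled here is a deviation. It does not rescue the sentence, because a rule on non-adherence operates only when there are deviations.

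Other stronger readings also fail:

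- **Randomisation is discarded.** It is lost only for patients whose treatment differs from allocation. With full adherence the two analyses are identical.
- **Error is inflated in both directions.** The pattern worked through biases only against CT. A different pattern could favour CT, but none is described or modelled.
- **Large error rates are to be expected.** The article gives no crossover rate or case mix. With 1 or 2 controls crossing, the effect is slight.
- **Intervention patients will miss scans because the scanner is unavailable.** The article does not discuss availability within the trial.

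The wording might also mean treatment group as allocated, with non-adherence reported as a caveat. That reading is possible but weaker, and it would need the same clarification. The promised presentation of non-adherence and the severity subgroups could make a problem visible, but they do not correct the main comparison. Nor is this a detail left to an analysis plan: the article states a rule, and the objection is to that rule.

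**Conclusion.** The point holds in conditional form. The article fixes a grouping rule that most naturally means treatment received, offers no analysis by allocation, and pairs the rule with unadjusted tests. If deviations follow fracture difficulty, the comparison is biased. Under the stated assumptions the bias runs from nothing at full adherence to about −8 points and 23% false rejections when 10 of 100 controls cross, and about half that bias when 5 cross. The likely harm is a missed benefit of CT or an apparent disadvantage. Confidence is high that the sentence needs changing. The size of the harm rests on an assumed case mix and crossover rate, and could be negligible.

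**What to change.** Replace the sentence in Evaluation of outcomes with:

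*All randomised patients will be analysed in the group to which they were allocated (intention to treat); an analysis by treatment received, with the number and reasons for non-adherence by arm, will be reported as a sensitivity analysis.*

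Apply the same grouping to the mid-study analysis. The Withdrawal section, which deletes the data of patients who withdraw, has to be reconciled with the reference to all randomised patients.

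The cost is small. No stated sample-size input changes. If crossover occurs, the estimated effect is slightly diluted. Allocation and whether a scan was done must be recorded for each patient. The assessment forms are not shown, so it cannot be confirmed that they already capture this; if they do not, a field has to be added.
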